#### Missing data

In the first instance missing follow-up Diabetes Knowledge Test Score data (Test B) will be assumed to be missing at random. Baseline checks will be carried out to test this assumption. Missing follow-up Diabetes Knowledge Test Scores (Test B) will be assumed to have remained unchanged for the intention to treat analysis. A complete case analysis will also be carried out excluding those missing follow-up test scores. A sensitivity analysis will be carried out to assess the difference between these analyses.

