### Sample size

We estimated that for a moderate effect size of 0.4 we needed a minimum of 100 participants in each arm (at a significance level of 0.5 and power of 80%). For an effect size of less than that, e.g. 0.3 the sample size increases to 176 per group. These needed to be inflated to account for drop out.

Since recruitment was to take place via online and print advertisement and registration, recruitment rates, learning material uptake and drop out were unknown, we decided to allow up to 1000 participants per country to complete the registration and baseline test until the cut off date for study recruitment. Obtaining a larger sample size than stated above will provide greater power for smaller effect sizes and allow the country subgroup analyses to have more power.

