### Statistical Analysis

All data will be checked during data cleaning for outlier data. Range checks from the online data collection will eliminate any out of range data. Any observed outliers will be checked with the database management team. Intention to treat analysis will be carried out for the primary analysis. Participants will be encouraged to complete Diabetes Knowledge Test B even if they have not spent as much time learning as they had planned. Complete case analysis will be used as a secondary analysis.

Summary statistics on participant assessment, eligibility, recruitment, withdrawal and dropout will be collated for both arms of the trial and form the CONSORT flow diagram for clinical trial reporting. The primary analysis will use Analysis of Covariance (ANCOVA) to compare the follow-up diabetes knowledge test scores between trial arms adjusting for baseline score as a covariate. This analysis makes distributional assumptions about the data and these will be checked prior to analysis. Variables used in the balancing algorithm will also be considered for inclusion as covariates. Secondary outcome analysis will compare the acceptability and practice change outcomes between trial arms. T-tests and Chi square tests will be used where appropriate for questionnaire items.

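### Baseline checks cannot test missing at random, and comparing two fixed analyses is weak evidence that the result withstands informative dropout in one arm

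*Protocol article*

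**What the plan says.** The Missing data section of the protocol article makes five statements in sequence:

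- As a starting point, "missing follow-up Diabetes Knowledge Test Score data (Test B) will be assumed to be missing at random".
- On how that starting point is to be verified: "Baseline checks will be carried out to test this assumption".
- For the primary analysis, missing Test B scores "will be assumed to have remained unchanged for the intention to treat analysis".
- A second analysis leaves out participants who have no Test B score.
- On how the two results are to be used: "A sensitivity analysis will be carried out to assess the difference between these analyses".

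The Statistical Analysis section gives the primary model, an ANCOVA to "compare the follow-up diabetes knowledge test scores between trial arms adjusting for baseline score as a covariate". It also says that the balancing variables will be considered as covariates. The Sample size section says that "recruitment rates, learning material uptake and drop out were unknown".

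**The concern.** Two statements promise more than the stated methods can deliver.

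First, missing at random means that, given the observed data, the chance of a missing Test B score does not depend on that unseen score. The article does not describe the baseline checks further. The natural reading is a comparison of participants with and without Test B on the recorded baseline variables: role, language, years since qualification, Test A score and registered-user status. Such a comparison contains no information about the unseen scores.

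Second, the sensitivity analysis is defined as the gap between two analyses. Each applies one fixed rule to both arms, and neither varies what non-completers might have scored. Similar results are likely to be read as robustness.

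Arm-specific dropout is plausible here, although not documented. Only the intervention arm is offered the DNAT, which takes 90 to 120 minutes and reports each learner's gaps. That could alter who goes on to sit Test B in that arm. What is at stake is the robustness statement that would accompany the primary result.

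**Working it through.** The plan states no figure on this point, so there is none to reproduce. The check asks how the planned baseline check and the planned comparison behave when dropout is informative.

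**1. Inputs**

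- From the article: the ANCOVA adjusted for baseline, the no-change rule, complete cases, 1:1 allocation, and effect sizes of 0.4 and 0.3 SD.
- Assumed, because the article does not give them: missing fraction m (20% to 50%); shift δ, the amount in SD by which non-completers score below their missing-at-random expectation; and the simulation settings in step 3.

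**2. Closed form: no true effect, informative dropout in the intervention arm only, m and mean gain alike in both arms**

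Let completers in the intervention arm score b above what their baseline predicts. For the whole arm to average zero, its non-completers must lie b(1 − m)/m below. Then δ = b + b(1 − m)/m = b/m, so b = mδ.

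- Bias of the complete-case ANCOVA: mδ.
- Bias of the no-change analysis: (1 − m)mδ, because only the observed fraction carries the surplus.

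With δ = 0.5 SD (assumed):

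| m | Complete case, mδ | No-change, (1 − m)mδ |
|---|---|---|
| 20% | 0.2 × 0.5 = 0.10 | 0.8 × 0.10 = 0.08 |
| 40% | 0.4 × 0.5 = 0.20 | 0.6 × 0.20 = 0.12 |
| 50% | 0.5 × 0.5 = 0.25 | 0.5 × 0.25 = 0.125 |

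Both biases have the same sign throughout.

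**3. Simulation**

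There were 1000 trials of 500 per arm, with true effect 0, baseline to follow-up correlation 0.6 and mean gain 0.5 SD in both arms. The log-odds of a missing Test B were −0.4 − 0.4 × baseline. Under informative dropout, 1.0 × the part of Test B not explained by baseline was also subtracted, in both arms or in the intervention arm only.

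| | Missing at random | Informative, both arms alike | Informative, intervention only |
|---|---|---|---|
| Missing, control / intervention | 40.5% / 40.4% | 41.5% / 41.6% | 40.6% / 41.6% |
| Baseline gap, missing minus observed (SD) | −0.38 | −0.35 | −0.36 |
| Baseline-by-arm term significant for missingness | 5% | 5% | 7% |
| Complete case: estimate (share significant) | 0.00 (7%) | 0.00 (4%) | +0.23 (92%) |
| No-change: estimate (share significant) | 0.00 (6%) | 0.00 (5%) | +0.13 (84%) |
| Full data: estimate (share significant) | 0.00 (6%) | 0.00 (5%) | 0.00 (5%) |

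The last column agrees with step 2. A complete-case bias of 0.225 at m = 0.416 implies δ = 0.225/0.416 = 0.54 SD, and (1 − 0.416) × 0.225 = 0.13.

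The baseline rows barely distinguish the mechanisms. In the last column the two planned analyses agree in direction and mostly in significance, yet both are wrong.

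**4. A gap between the analyses is not diagnostic either**

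Suppose scores are missing at random, the true effect is 0.4 SD and both arms lose the same fraction. Complete cases then target 0.4, while the no-change analysis targets 0.4 × (1 − m): 0.32 at 20%, 0.24 at 40% and 0.20 at 50%. The imputation rule alone creates the difference.

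**5. What a tipping-point analysis would report**

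A shift δ in one arm cancels a missing-at-random estimate d when δ = d/m.

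| m | d = 0.4 | d = 0.3 |
|---|---|---|
| 20% | 2.0 SD | 1.5 SD |
| 30% | 1.33 SD | 1.0 SD |
| 40% | 1.0 SD | 0.75 SD |
| 50% | 0.8 SD | 0.6 SD |

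These shifts bring the estimate to zero; losing statistical significance would take less. The planned comparison produces no figure of this kind.

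**The case against.** The strongest reply has five parts.

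- **Nothing hangs on the check.** The section has no pass or fail rule, and both analyses are run whatever the check shows. The no-change imputation does not rest on missing at random. This stands. A reader might infer that a failed check would divert the analysis, or that the primary estimate depends on the check; the article supports neither.
- **The two analyses do make different assumptions.** No-change imputation is itself one fixed departure from missing at random, so the comparison does probe one alternative. This also stands. A reader might infer that agreement says nothing at all about informative dropout, which is too strong. It is weak evidence, from a single scenario that does not vary the rule by arm.
- **The sizes are assumed.** The article gives neither m nor δ, the whole shift is placed in one arm, and mδ describes a complete-case or missing-at-random estimate. The no-change estimate moves less. All of this is accepted.
- **Heavy dropout is not documented.** The article says only that it was unknown. It describes professional-development credit, a certificate, free access to products, reminders and encouragement to sit Test B regardless of learning time. This is accepted too.
- **A tipping-point analysis belongs in an analysis plan that is not shown.** This does not dispose of the point. The article itself says what the baseline checks will test and defines what the sensitivity analysis compares; both statements can be judged as written.

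**Conclusion.** The point holds in a limited form. The sentence on baseline checks is wrong as stated: they can refute missing completely at random and suggest predictors, and no more. The sensitivity analysis, as defined, is one alternative scenario with the same rule in both arms, so agreement between its two parts is weak evidence of robustness.

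The illustrated false effect of +0.23 SD (complete cases) and +0.13 SD (no-change) needs three assumptions: dropout near 40%, dropout informative in one arm only, and a shift of about 0.54 SD. The shares of significant results also depend on the assumed 500 per arm. With informative dropout alike in both arms and no true effect, neither analysis is biased.

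A reader might go further and conclude that the primary result will be biased by a stated amount. The documents do not support that, because they give neither the dropout rate nor any shift. What needs correcting is the assurance attached to the result.

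**What to change.** In the Missing data section, replace the sentence on baseline checks and extend the one on sensitivity analysis, for example:

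> Baseline variables associated with a missing Test B score will be identified and included as covariates in the ANCOVA or as predictors in an imputation model. The no-change and complete-case results will be compared. In addition, starting from a missing-at-random estimate, the scores of non-completers will be shifted by a range of deltas set separately for each arm. We will report how far below expectation non-completers in one arm must score to overturn the conclusion.

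Part of this is already provided for, since the ANCOVA adjusts for Test A and the balancing variables are under consideration as covariates.

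Usage recorded by the LMS needs care. It is measured after randomisation and may be affected by allocation, because the DNAT recommends modules. It may serve only as an auxiliary variable in an imputation model, by arm. It must never be a covariate in the analysis model, where it could adjust away part of the intervention effect.

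The cost is two sentences, a short analysis on data already held, and one extra table.

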### Outcome measures

#### Primary Outcome measure

##### Diabetes Knowledge Test

The Diabetes Knowledge Test contains 20 multiple choice questions (in the format of single best answer out of five possible options). There are two versions of the Diabetes Knowledge Test – Test A and Test B. All learners will receive the same baseline Diabetes Knowledge Test (Test A) prior to randomisation. Test B is a slightly different test of equal difficulty to be administered at the end of the learning period. The primary outcome will be Diabetes Knowledge Test scores at four months. Note-while the knowledge tests contain 20 items, only 19 items will be used in the knowledge test scores as one of the items in each test is a "rogue" item not on diabetes.

The Diabetes Knowledge Tests were developed from the same large pool of calibrated items as the DNAT but there is no overlap between the DNAT and the knowledge tests.

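### The primary analysis scores every missing Test B as no change, which the plan's missing-at-random assumption does not imply and which can dilute or bias the effect

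*Protocol article*

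**What the plan says.** The Statistical Analysis section states "Intention to treat analysis will be carried out for the primary analysis" and gives the model: "The primary analysis will use Analysis of Covariance (ANCOVA) to compare the follow-up diabetes knowledge test scores between trial arms adjusting for baseline score". It adds that the variables used to balance the randomisation will be considered as covariates, and "Complete case analysis will be used as a secondary analysis".

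The Missing data section opens with "In the first instance missing follow-up Diabetes Knowledge Test Score data (Test B) will be assumed to be missing at random", followed by "Baseline checks will be carried out to test this assumption". Its next sentence is "Missing follow-up Diabetes Knowledge Test Scores (Test B) will be assumed to have remained unchanged for the intention to treat analysis". It then plans a complete-case analysis and a comparison of the two results.

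The Sample size section says that "recruitment rates, learning material uptake and drop out were unknown". No dropout rate, expected learning gain or Test A to Test B correlation is given anywhere.

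**The concern.** The assumption and the imputation rule make different claims about the same people. Under missing at random, a participant without Test B has, on average, the score of a completer in the same arm with the same observed data. Setting the score to the Test A value gives that participant zero gain whatever the completers did. The analysis that decides the trial therefore does not rest on the assumption stated just before it.

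This matters because dropout in an online trial may be large and is declared unknown. Both arms receive the same Diabetes Learning Modules, so some gain in each arm is plausible. Only the intervention arm is asked for a further 90 to 120 minutes on the DNAT, so dropout may also differ by arm. The primary estimate would then partly measure who returned for Test B.

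**Working it through.** **Inputs.** From the protocol: 1:1 allocation, ANCOVA on Test B adjusted for Test A, target effect 0.4 SD, 100 per arm before dropout, and a ceiling of 1000 registrants per country. Assumed, because the protocol is silent: dropout of 20% to 50%, mean gain of 0 to 0.5 SD, correlation 0.5, SD 1.

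**Step 1: the plan's own figure.** A two-sample t-test with two-sided alpha 0.05 and 80% power needs 99.1 per arm for 0.4 SD and 175.4 for 0.3 SD. Rounded up, these are the stated 100 and 176. (The printed significance level of 0.5 would give 29 and 52, so it looks like a misprint; that is a separate matter.) Inflating 100 for 40% dropout gives 100/0.6 = 167 per arm, used below as an example.

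**Step 2: what the rule estimates.** Let p1 and p0 be dropout in the DNAT and control arms, g1 and g0 the mean gains, and delta = g1 - g0. Non-completers contribute zero change, so with balanced baselines the expected contrast is

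(1 - p1) g1 - (1 - p0) g0 = (1 - p1) delta + g0 (p0 - p1).

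This is exact when dropout within an arm does not depend on Test A. It is a close approximation when dropout does depend on Test A: simulation gave 0.237 against 0.24 from the formula, and -0.117 against -0.10.

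**Step 3: equal dropout.** The second term vanishes and the effect is multiplied by (1 - d). For delta = 0.40 SD:

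| Dropout, both arms | Formula | Simulated, no-change rule | Simulated, observed-data ANCOVA |
|---|---|---|---|
| 20% | 0.32 | 0.325 | 0.407 |
| 30% | 0.28 | 0.277 | 0.396 |
| 40% | 0.24 | 0.241 | 0.402 |

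At 40% dropout and 167 per arm, 95% interval coverage of the true 0.40 is about 55% and ANCOVA power is about 79%, against about 95% and 91% for ANCOVA on observed scores. With no true effect, type I error is kept (4.3% at 30% dropout).

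**Step 4: unequal dropout, true effect 0.40 SD, gain 0.5 SD.**
- DNAT 40%, control 20%: 0.6 × 0.40 + 0.5 × (0.2 - 0.4) = 0.14 (simulated 0.137).
- DNAT 20%, control 40%: 0.8 × 0.40 + 0.5 × (0.4 - 0.2) = 0.42 (simulated 0.42).

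**Step 5: unequal dropout, no true effect.** The contrast reduces to g0 (p0 - p1).

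| Dropout, DNAT v control | Gain | Per arm | Bias | Type I error |
|---|---|---|---|---|
| 50% v 40% | 0 | 500 | 0 | about 5% |
| 50% v 40% | 0.2 SD | 500 | -0.02 SD | 7-8% |
| 45% v 40% | 0.5 SD | 500 | -0.025 SD | about 8% |
| 50% v 40% | 0.5 SD | 500 | -0.05 SD | about 19% |
| 50% v 40% | 0.5 SD | 1000 | -0.05 SD | 32-34% |

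Observed-data ANCOVA stayed at about 4% to 6% throughout. As a hand check, the standard error at 1000 per arm is 0.033, so at 500 it is about 0.033 × √2 = 0.047. A bias of 0.05 shifts the test statistic by 0.05/0.047 = 1.07, and P(Z > 1.96 - 1.07) = P(Z > 0.89) is about 19%. At 1000 per arm the shift is 0.05/0.033 = 1.52, giving about 33%. One thousand per arm would need two countries to fill their cap: 2 × 1000 / 2.

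**The case against.** The best defence is that the plan already contains a suitable analysis. Complete-case ANCOVA adjusted for baseline is prespecified, the balancing variables may be added, and the two results will be compared. A reader would see both. The words "In the first instance missing follow-up Diabetes Knowledge Test Score data (Test B) will be assumed to be missing at random" could also be read as the basis for the complete-case analysis only, with no change as a deliberately cautious intention-to-treat rule. And if non-responders truly learned nothing, no change is right on average; since uptake is declared unknown, nobody can say that many of them used the modules.

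Part of this stands. The complete-case analysis is a real mitigation, and the dispute is over which analysis leads. But the plan gives no rule for choosing if they disagree, and baseline checks cannot confirm missing at random. Nor is the rule reliably cautious, because higher dropout in the control arm moves the estimate in favour of the DNAT.

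Four stronger readings are tempting and are not supported:
- **That imputed scores make the standard error too small.** In simulation at 1000 per arm the reported value (0.033 to 0.034) matched the actual spread of the estimate (0.033). The poor coverage comes from the shifted estimate.
- **That power falls to about 59% at 40% dropout.** That figure comes from an unadjusted t-test at 0.24 SD. The planned analysis is ANCOVA, with about 79% at the assumed correlation.
- **That any difference in dropout biases the result.** The added bias needs a non-zero mean gain; at zero gain there is none.
- **That carrying a Test A score to Test B is itself an error.** The protocol states that "Test B is a slightly different test of equal difficulty to be administered at the end of the learning period".

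**Conclusion.** The point holds and the plan is wrong as written: its primary analysis uses a rule that its stated missing-data assumption does not imply. Under that assumption, equal dropout costs effect size, coverage and some power but leaves type I error intact. Unequal dropout with a non-zero gain biases the estimate in either direction, and the resulting type I error grows with sample size. It is slight for a small gain or a small dropout gap, and serious for a 10-point gap with a 0.5 SD gain.

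The sizes depend on the assumed dropout, gain and correlation. The direction and form of the distortion follow from the formula. If scores are in truth not missing at random, observed-data ANCOVA may be biased too, which is a reason to keep the no-change result as a sensitivity analysis.

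**What to change.** Before data are exported, swap the roles of the analyses. Make the primary analysis one that is valid under the stated assumption, in either form:
- ANCOVA on observed Test B scores, adjusted for Test A and the balancing variables (language, doctor or nurse, years since qualification, registered-user status); or
- multiple imputation of Test B separately by arm, using those variables and the usage data that the learning management system and link tracking already capture, followed by the same ANCOVA with Rubin's rules.

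Keep the no-change analysis as a labelled sensitivity analysis and report dropout by arm beside it. No new data are needed. The cost is a wording change, a little more analysis work and a wider confidence interval, which is wider because the analysis targets the undiluted effect.

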#### Subgroup analysis

Planned subgroup analyses involve the investigation of the learning outcomes within language group. This will be achieved by the addition of an interaction term to the primary analysis.

### Trial organisation

The principal investigator will co-ordinate the trial with the assistance of the Chief Information Officer (CIO) at BMJ OnExamination and chair regular steering group meetings with the research co-investigators. The co-investigators will regularly monitor the study's progress. SEWTU will provide input at management group level for the design and conduct of the study together with statistical input in the design of the websites to ensure quality data collection. SEWTU will validate the data collection and randomisation together with the CIO from OnExamination. The CIO is responsible for the management, recording, and storage of data. The study protocol is managed centrally by the CIO and any protocol deviations will be documented and reviewed by the steering group at regular intervals.

#### Data Quality Assurance

All study tests and surveys will be administered to participants online and the data collected centrally on an independent platform. Participants will be asked for their email address at enrolment and will be prevented from enrolling more than once using the same email address. This should prevent the majority of duplication. Shortly after randomisation a check will be made for those that enrolled with identical firstnames, surnames, and language choice but different email addresses. The first registered email address that had a completed baseline Diabetes Knowledge Test will be assigned as their account and any other email addresses disabled. We will then write to these participants to tell them that we noticed they had registered more than once and that they should use the selected email address from now on as we will disable the other(s).

#### Publication Policy

We will submit the results of the trial for publication in a biomedical journal irrespective of outcome.

#### Timetable

February to March 2009: Recruitment of learners. Registered learners gave consent and were administered Diabetes Knowledge Test A

25^th ^to 31^st ^March 2009: Stratified randomisation

1^st ^April – 31^st ^July 2009: 4-month learning period

1^st ^August 2009: Administration of Diabetes Knowledge Test B and the Acceptability Survey

1^st ^September 2009: Administration of the Practice Change Survey

25^th ^September 2009: Close of data collection

26^th ^September 2009: Data to be given to independent statisticians for analysis

